## Methods/design

This study is a three-arm, cluster randomised feasibility trial with a parallel group design. The novel RECALL classroom programme will be compared to an existing intervention (ALP, the active control) and education as usual (the no intervention control). The delivery of the interventions at the classroom level necessitates the use of a cluster design for this study [34, 35] with each school constituting a cluster. The experimental RECALL programme and the active control intervention will be delivered by health professionals from the multi-disciplinary RISE teams once per week. Thus, they will demonstrate the programmes for the teachers who will then provide two further practice sessions during the week.

Children’s outcomes will be measured at two time points (baseline and 1-week post-intervention). The protocol has been developed according to the SPIRIT 2013 Statement [36] recommendations for protocol items for clinical trials and the CONSORT 2010 extension to cluster randomised pilot and feasibility trials [37]. Throughout the trial, a process evaluation will explore the factors that could impact on the internal and external validity of a future CRT and the intervention’s logic model for RECALL will be refined [38, 39]. Figure 1 shows the flow chart of the study and Fig. 2 illustrates the timing of all trial processes.

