### Sample size and participants

As this is a feasibility study, and the purpose is to explore the acceptability of the intervention rather than its effectiveness, a formal a priori power calculation has not been conducted [41]. The results will not be used to estimate the sample size, intra-cluster correlation or treatment effects for a definitive trial because, in the case of cluster randomised feasibility trials, these can be unrealistic and misleading [42, 43]. Therefore, the number of clusters and individual participants to be recruited has been selected in order to assess the acceptability and feasibility of RECALL and the outcome measures for children’s WM, attention and language skills.

At the cluster level, six schools in areas of LSES will be recruited in total. One class of children in year one (*n = ~* 30) will participate in each school (total: *n =* ~ 180 children). Two classes will receive the RECALL programme, two will receive the active control intervention (ALP) and two will receive education as usual. In the schools allocated to the to RISE and ALP groups, all of the children in the participating classes will receive the interventions. Health professionals from the RISE teams (SLTs, OTs, PTs and SEBs) will be recruited to deliver the RECALL and active control interventions.

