#### Stratification of children

At the individual level, ten children, their parents/guardians and teachers will be recruited in each class to complete the outcome measures (total sample: *n =* 60 children). Due to the age of the children involved in this study (4–5 year olds), the number of standardised measures available, particularly of WM and attention, is limited. To determine the appropriateness and acceptability of the outcome measures that have been selected, they will be trialled with children representing the typical range of ability in a year one class. Hence, we will use stratified purposeful sampling [44]. Teachers in each class will identify children in three sub-groups/strata: (1) children about whom they have concerns around listening and communication skills but do not have a diagnosed developmental or learning difficulty (*n =* 5); (2) children with diagnosed developmental or learning difficulties (*n =* 2); and (3) typically developing children who do not have any identified listening and communication problems as recognised by the teachers (*n =* 3 per class). Children considered to be typically developing, within areas of social disadvantage, will be included due to the high incidence of speech, language and communication needs in this population [3].

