### Randomisation and allocation

The six schools will be randomised to each arm of the trial: two will receive RECALL; two will receive the active control intervention (ALP); and two will receive education as usual. This will be conducted by the schools’ names being placed in opaque, sealed envelopes which will be selected by an independent person from within the lead researchers’ institute. This process has been deemed as introducing a low risk of bias in allocation concealment [51]. Randomisation will occur after baseline data collection with the children. As previously indicated, children will be selected for outcome measurement using stratification. The teacher will sort the names of all those whose parents provide written informed consent into the three strata previously specified. If more than the required number in each sub-group consent, the participants will be randomly selected using the same process of placing names in opaque envelopes.

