
### Data analysis

The feasibility data will be analysed and reported descriptively using means, frequencies and percentages. The data will be summarised and presented graphically. A CONSORT flow diagram will be used to report the response, recruitment and retention rate of clusters and individual participants at each point of the study. Where available, reasons for attrition and loss to follow-up will be reported.

Regarding the data obtained from the outcome measures completed with the children, statistical significance of treatment effects will not be analysed as this study would be under-powered for this purpose. However, between group comparisons will be conducted to inform the statistical model for the future trial. This will include two elements: (1) a series of one-way analyses (ANOVAs) of the baseline data of children’s standardised scores on the working memory (AWMA), attention (NEPSY subtests) and language measures (CELF-P) to investigate pre-intervention group differences; and (2) a series of analyses of covariance (ANCOVAs) to investigate post-intervention group differences). As the standardised assessments of WM, language and attention will be repeated within a short time-frame, results from the education as usual group will be used to examine test-retest effects. Qualitative analysis of the data gathered in the semi-structured interviews will be carried out using Braun and Clarke’s (2006) thematic analysis [95].

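### The ANOVAs and ANCOVAs named for the children's scores have no term for school, although six schools are randomised, two per arm, so any interval or p-value from them would be too precise

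*Protocol article*

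**What the plan says.** The Methods/design section gives the reason for clustering: "The delivery of the interventions at the classroom level necessitates the use of a cluster design for this study", "with each school constituting a cluster". Sample size and participants states that "six schools in areas of LSES will be recruited in total". Randomisation and allocation splits them: "two will receive RECALL; two will receive the active control intervention (ALP); and two will receive education as usual". Under Stratification of children, "ten children, their parents/guardians and teachers will be recruited in each class to complete the outcome measures", which gives 60 children.

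Data analysis first says that "statistical significance of treatment effects will not be analysed as this study would be under-powered for this purpose". It then announces between-group comparisons meant to inform the statistical model of the future trial. These have two elements: (1) one-way ANOVAs of the children's baseline standardised scores, and (2) "a series of analyses of covariance (ANCOVAs) to investigate post-intervention group differences". No section mentions a school term, a random effect, a school-level summary or a cluster-robust variance for these comparisons. No ICC is given, and no confidence intervals or standard errors are promised.

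Sample size and participants adds that "The results will not be used to estimate the sample size, intra-cluster correlation or treatment effects for a definitive trial".

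**The concern.** When schools are randomised, an arm comparison is a comparison of schools. With two schools per arm, an ordinary difference between schools (teacher, intake, class climate) is hard to tell apart from a difference between arms. A one-way ANOVA has group as its only factor. An ANCOVA without further specification adds a covariate but no school. Both then take their error mainly from differences between children within schools and use about 56 residual degrees of freedom, when six schools in three arms supply 3.

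Two things are at stake. First, any interval, F-test or p-value printed from these models would present school-to-school variation as a precise arm difference, both at baseline and after the intervention. Second, the comparisons are meant to inform the model of a definitive trial that the article describes as cluster randomised. A model that leaves out the cluster cannot do that.

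**Working it through.** **Inputs from the article.** 6 schools, 3 arms, 2 schools per arm, m = 10 measured children per school. The article's own total reproduces: 6 × 10 = 60 children, 20 per arm (strata 5 + 2 + 3 = 10 per class).

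**Assumptions.** The ICC is not stated, so a range of 0 to 0.20 is used. Intervals are two-sided 95%.

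**Degrees of freedom.** Child-level ANCOVA: 60 − 3 arms − 1 covariate = 56, t = 2.003. School-level: 6 − 3 = 3, t = 3.182. (With no covariate the child-level figure is 57; the effect on t is negligible.)

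**Interval width, unadjusted arm difference.** Design effect DE = 1 + (m − 1) × ICC = 1 + 9 × ICC. Ratio of child-level to school-level standard error = 1/√DE. Ratio of interval widths = 2.003 / (3.182 × √DE).

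| Assumed ICC | DE | Effective n (60/DE) | SE ratio | Interval-width ratio |
|---|---|---|---|---|
| 0 | 1.00 | 60 | 1.00 | 0.63 |
| 0.02 | 1.18 | 51 | 0.92 | 0.58 |
| 0.05 | 1.45 | 41 | 0.83 | 0.52 |
| 0.10 | 1.90 | 32 | 0.73 | 0.46 |
| 0.20 | 2.80 | 21 | 0.60 | 0.38 |

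The width ratio falls to one half at an ICC of about 0.065. The SE ratio does so only at about 0.33.

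**The same on a score scale (SD of 15 assumed).** Child-level half-width: 15 × √(2/20) × 2.003 = 9.5 points. School-level half-width: 3.182 × √(225 × [ICC + (1 − ICC)/10]) = 18.2, 20.8 and 25.3 points at ICC 0.05, 0.10 and 0.20.

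**Coverage (40,000 simulated trials per ICC, no covariate).** The child-level 95% interval covers the true difference in 94.7%, 92.7%, 89.7%, 83.7% and 73.8% of trials at ICC 0, 0.02, 0.05, 0.10 and 0.20. The school-level interval stays at 95% throughout.

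**False-positive rate of the ANCOVA.** This was simulated under no effect, with 3 × 2 × 10 children and a within-school baseline-to-follow-up correlation of 0.7. The result depends strongly on how well a school's own effect at baseline predicts its effect at follow-up, because baseline adjustment removes the part that persists.

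| School-level correlation | ICC 0.05 | ICC 0.10 | ICC 0.20 |
|---|---|---|---|
| 0 | 25% | 41% | 58% |
| 0.7 | 12% | 21% | 35% |
| 0.9 | 8% | 12% | 21% |
| 1.0 | 6% | 7% | 9% |

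The nominal rate is 5%. A separate rerun agreed to within about one percentage point.

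**The case against.** **The article disclaims inference.** It says significance of treatment effects will not be analysed and that the results will not be used to estimate treatment effects or the ICC for the definitive trial. Under Criteria for proceeding to a full CRT, progression rests primarily on recruitment, retention and completion of measures. This stands, and it limits the harm to a secondary analysis. It does not remove the point. The ANCOVAs are still named, nothing says their tests will be suppressed, and the reason given for not testing is low power. Low power concerns missed effects, whereas ignoring clusters produces spurious ones.

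**Independence is inferred, and a fuller plan could add school.** The inference is fair but remains an inference. The point is more than an omission, however, because the article names methods, and as named they do not fit the design.

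**The size depends on assumptions.** This stands. A reader might infer that every group difference will be shown with error bars half the correct width or less. The article does not support that: it plans no error bars and gives no ICC. The ratio is above one half at ICCs of 0.02 and 0.05, and the 0.63 at ICC 0 comes from the t multiplier alone. The ratios also compare typical widths. In the simulation at ICC 0.05, the child-level interval was at most half the school-level one in 36% of trials and wider than it in 14%. Baseline and follow-up are only weeks apart in the same classes, so high persistence of school effects, and hence a false-positive rate towards the lower end, is plausible.

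**There is no clear self-contradiction.** A reader might say that the article forbids effect analysis and then orders it. The text separates significance testing from comparisons that inform a model, and an ANCOVA can supply adjusted means without a test. The wording is awkward but can be reconciled.

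**Conclusion.** The point holds as a moderate issue. The analyses named for the children's scores, at baseline and after the intervention, make no allowance for the randomised unit, so any interval or p-value they yield would overstate precision.

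For an unadjusted arm difference, the child-level interval would be about 0.58 to 0.38 of the school-level width over assumed ICCs of 0.02 to 0.20, with 3 degrees of freedom as the reference. At ICC 0.10 the ANCOVA would reject a true null in about 7% to 41% of trials as the school-level correlation goes from 1 to 0, and in about 21% at a correlation of 0.7. ICCs may well differ between measures.

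The failure to serve the stated modelling purpose needs no assumed ICC. A reader might go further and conclude that the feasibility trial's main result is unsound, or that an unclustered model will pass into the definitive trial. The article does not support either: its primary objectives concern acceptability and feasibility, and it calls the future study a cluster randomised trial throughout.

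**What to change.** In Data analysis, replace both element (1) and element (2). Suggested text: *Baseline and post-intervention scores will be summarised by school and by arm (n, mean, SD), without p-values. If arm differences are shown, they will come from an analysis with the school as the unit, for example baseline-adjusted school means compared between arms, with 95% confidence intervals on 3 degrees of freedom.*

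Purely descriptive summaries by school would also be enough; the two-stage comparison is one acceptable option among several. Changing only the ANCOVAs would leave the baseline ANOVAs with the same defect.

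The cost is wording only, with no new data. The drawback is that any interval shown becomes much wider: on the assumed SD-15 scale, about ±21 points at ICC 0.10 compared with ±9.5. That is the precision two schools per arm can give.

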### Process evaluation

A process evaluation will be conducted throughout the study to support an understanding of how the trial processes relate to the context within which RECALL will be implemented [80]. The cluster and individual level data on the acceptability and feasibility of RECALL will be integrated with the qualitative findings and observations of cluster characteristics using the model proposed by Grant et al. [96]. Through this, the barriers and facilitators to implementation will be explored and the intervention logic model developed during the co-production phase will be refined.

### Criteria for proceeding to a full CRT

The primary factor for consideration as to whether to proceed to a full trial will be the feasibility data pertaining to recruitment and retention rates and the completion of outcome measures. However, strict thresholds for progression have not been set as these factors can be influenced by contextual variations that may not impact on a future trial [42, 97]. Rather, the decision to proceed to a main trial will be made along by the research team in collaboration with the Trial Steering Committee. Solutions to any problems observed in the feasibility trial will be sought through four potential options suggested by Bugge et al. [98]: (1) adapt the intervention, (2) adjust the context within which the intervention would be delivered, (3) amend elements of the trial design or (4) implement a combination of all of these actions.

### Monitoring

#### Trial steering committee

The conduct of this trial will be overseen by a Trial Steering Committee (TSC) that includes experienced researchers, key stakeholders from the health and education sectors in NI and service users. This group has been involved in the design of the trial and will meet at an interim point to review the progress towards the trial aims and to monitor the safety and well-being of all participants. Due to the nature and purpose of the primary data to be collected in this study (feasibility and acceptability measures), a Data Management Committee is not deemed necessary at this stage but will be established prior to the definitive CRT.

#### Modifications

Any modifications to the study protocol such as the eligibility criteria, recruitment procedures or outcome measures will only be carried out in agreement with the TSC. The changes made and reasons underlying them will be carefully recorded as these could be vital to the design of the future trial.

#### Stopping guidelines

Any adverse events occurring in the course of the trial will be carefully recorded and reported to the TSC, although this is not anticipated given the low risk nature of the study. The TSC will be contacted in this unlikely event and the trial may be discontinued. The study may also be discontinued if both schools in the RECALL arm of the trial withdraw. In the case of the trial being discontinued, all of the other active participants will be informed. The active control intervention may be continued as part of routine practice by the health professionals but no further data would be collected from the children for outcome measurement. The parents would be informed accordingly.

#### Ethical considerations

As noted, this is a low-risk study in that no additional potential harm is associated with the research compared to the everyday activity of the participants. The main ethical considerations relate to the welfare of children, parental consent and the children’s capacity to assent, and the maintenance of confidentiality. The schools’ policies regarding health and safety and child protection will be obtained in advance by the research team and adhered to throughout the trial. All members of the research team will hold valid Access NI Enhanced Disclosure Certificates^3^ confirming they are permitted to work with children in compliance with NI legislation. Through the whole-class sessions, it is possible that children with neurodevelopmental difficulties may be identified by the health professionals. In this instance they will advise the teacher of an appropriate service to which the child could be referred and ask them to seek parental consent prior to making a referral. Children who already attend another service will continue to receive this support during the trial. The procedures for obtaining parental consent in this study have been designed according to guidance provided by the Health Research Authority (2017) [50] (see consent section). All information/data obtained during the study will remain confidential and will be held in accordance with the General Data Protection Regulation (EU) 2016/679. Aside from the initial consent forms, all further material will be identified by unique number only, with no identifying information. The procedures used to ensure anonymity and confidentiality may be subject to audit through Ulster University’s annual audit programme.

#### Dissemination

The findings from this trial will be disseminated to all of the participants at a local level through informal networks in the first instance. At a national and international level, the results will be disseminated through conferences and publications in professional literature and peer-reviewed journals prior to the final design and conduct of a full CRT.

## Discussion

To our knowledge, RECALL is the first theoretically underpinned, multi-component, whole-class intervention that specifically aims to enhance WM, attention and language skills in 4–5-year-old children through activities applied within their everyday context. This study responds to calls for ecologically valid approaches to WM intervention for young children [28, 99] and the testing of creative approaches for children with low-language ability who are at risk of academic underachievement and poor employment prospects [8, 9].

A realist perspective underpins all stages of this research, influencing the intervention development, trial design and process evaluation. This approach recognises the impact of context on the implementation of interventions in real-life settings [39, 52, 53], which has been lacking in WM research to date. Therefore, the findings from this feasibility study will be of interest to researchers and practitioners interested in implementing WM interventions in the classroom.

In particular, the observations of RECALL being delivered in the classroom will allow investigation of whether it is possible for WM interventions to be delivered in the classroom with fidelity to their design and dosage. Key in this examination will be whether the executive-loaded nature of the trained tasks is maintained in their implementation. The inclusion of qualitative data in the process evaluation is a strength of this feasibility trial. This will allow us to explore participants’ views on the acceptability of RECALL and, crucially, the reasons for any differences between the intervention model and their fidelity to it. Thus we will be able to identify issues that may impact on the external and internal validity of a large-scale CRT.

The study design takes cognisance of the previous criticisms of the methodological quality of previous WM research [23–25], through the inclusion of an active control group (receiving a comparable intervention in terms of structure and dosage) and the blinding of outcomes assessors. The findings from this feasibility study will inform whether it can be scaled-up into a full CRT to evaluate the clinical and cost-effectiveness of RECALL.

## Trial status

Recruitment will commence in December 2018.

## Abbreviations

ALP: Attention and Listening programme
CA: Classroom assistant
CRT: Cluster randomised trial
HSCT: Health and Social Care Trust
LSES: Low socio-economic status
NI: Northern Ireland
OT: Occupational therapist
PT: Physiotherapist
RA: Research assistant
RECALL: Recall to Enhance Children’s Attention Language and Learning
RISE: Regional Integrated Support for Education
SEB: Social Emotional and Behaviour Specialist
SLT: Speech and language therapist
STM: Short-term memory
TSC: Trial Steering Committee
WM: Working memory
